### Randomization and allocation concealment

After the baseline assessment, eligible participants were randomly assigned to the Tai Chi group and the waiting list group in a ratio of 1:1. The random allocation sequence was generated by an independent statistician using the PLAN procedure of the statistical software SAS 9.1. The random grouping sequence was hidden by opaque and sealed letters and managed by an independent research assistant who knows nothing about the recruitment, evaluation, and intervention of the participants. The eligible participants were informed of their allocation result by the independent research assistants via telephone.

### Blinding

In this study, it is impossible to blind the Tai Chi coaches and participants. However, statistician blindness and evaluator blindness were used in this study. Two levels of blindness would be used in this study: the first level of blindness with the letters “A” and “B” to represent the groups assigned by the participants, and the second level blind bottom with “A” and “B” to represent intervention measures, such as “Tai Chi group” and “waiting list group”. At the end of the trial, the data were entered into the database according to the participants’ codes. After the data were checked, the database was closed, and the first-level unblinding is performed to determine which group of participants were assigned to “A” and “B”. After completing all the data analysis, the second-level of unblinding is performed to determine whether the subjects were assigned to the Tai Chi group or the waiting list group.

### Intervention

#### Tai Chi group

The Tai Chi adopted in this study is the 24 forms of simplified Tai Chi training, which are recommended by the General Administration of Sport of China as a popular health sport [40]. Qualified coaches who have been teaching Tai Chi for more than 5 years will teach participants the correct Tai Chi training throughout the intervention period. In addition, all the coaches completed the required research and human protection training before starting the intervention course.

Participants in the Tai Chi group will receive 12 weeks of concentrated Tai Chi training, three times a week, a total of 36 times, each for 60 min including 10-min warmups, 45 min Tai Chi training, and 5 min cool down. The training will be held in the gymnasium of Fujian University of Traditional Chinese Medicine or Community activity center or park.

#### Waiting list group

The participants in the waiting list group will be requested to maintain their routine lifestyle and did not take any intervention measures. After the study (24 weeks), participants in the waiting list can choose to participate in Tai Chi training or accept other interventions.

All participants will be informed to record their daily activities or exercise information during the study to observe any effects of normal physical activity.

### Follow-up period

After 12 weeks of intervention, all participants will begin an additional 12 weeks of unsupervised follow-up period. The participant will resume their routine lifestyle during the follow-up period. After 12-week follow-up period, primary and secondary outcomes will be remeasured.

### Outcome measurement

The variables of this trial include basic characteristics, primary outcomes, secondary outcomes, and exploratory outcomes. The basic characteristics were measured at baseline (1–2 weeks before randomized) via a questionnaire. Primary and secondary outcomes were measured at baseline, the end of the intervention (12 weeks after randomization), and the end of the follow-up period (24 weeks after randomization). Exploratory outcomes were measured at baseline and the end of the intervention period (12 weeks after randomization). All outcomes are evaluated by the experienced assessors who do not know the allocation results of participants.

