### Sample size estimation

In this study, the influence of Tai Chi on the depressive symptom of young adults with subthreshold depression was observed. When estimating the sample size, PHQ-9 and HAMD-17 were used as the main effect indicators to calculate the required sample size. Besides, the larger sample size was used as the sample size of this study.

The sample size estimation was based on the improvement in PHQ-9 (The 9-item Patient Health Questionnaire) scores. According to relevant published literature [22], the mean and its SD of PHQ-9 scores after the 8 weeks of mindfulness-based Tai Chi training for subthreshold depression adolescents were 6.03 and 2.18 points, respectively, while the mean and its SD of PHQ-9 scores in the control group were 8.10 and 2.52 points, respectively. According to the above results, a sample size of 58 participants was calculated to sufficiently detect the target effect size (0.879) with a type 1 error of 5% (*α* = 0.05) and 90% power (*β* = 0.10) by Gpower V.3.1.9.2 software. Assuming a dropout rate of 10%, a total of 64 participants are necessary, with 32 participants in each group.

Simultaneously, according to the research [21], the total score of HAMD-17 obtained by regular Tai Chi training to improve patients with major depressive disorders was 9 ± 5 points while the HAMD-17 score of control group patients with major depressive disorders was 15 ± 7 points. Based on the above results, a sample size of 46 participants was calculated to sufficiently detect the target effect size (0.986) with a type 1 error of 5% (*α* = 0.05) and 90% power (*β* = 0.10) by Gpower V.3.1.9.2 software. Assuming a dropout rate of 10%, a total of 52 participants are necessary, with 26 participants in each group.

Since the sample size calculated using PHQ-9 as the result indicator is more than HAMD-17, this study chose PHQ-9 as a basis to estimate the sample size of this study, and a total of 64 subjects were recruited.

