#### Primary outcome measures

The primary outcome measure changes in the PHQ-9 and HAMD-17 between baseline and 12 weeks.

The 9-item Patient Health Questionnaire (PHQ-9) is a self-report measure used to assess 9 depressive symptoms according to the DSM-IV depression criteria. It has a total of 9 items, each with a score of 4 points (0–3 points) and the total scores’ range of 0–27 points. This score can be used to describe the patient’s symptoms, divided into five categories: none (0–4), mild (5–9), moderate (10–14), moderately severe (15–19), and severe (20–27) [41]. PHQ-9 has been translated into Chinese, and its Chinese version has demonstrated reliability and validity [42].

The 17-item Hamilton Depression Scale (HAMD-17) [43] is the most widely used scale in the clinical evaluation of depression, including17 items that assess function in five areas: anxiety/somatization, retardation, cognitive impairment, sleep disturbance, and weight change. Higher scores indicate more severe depression.

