Cortisol has circadian rhythm and pulsation; the reliability of evaluating the functional status of the HPA axis only by collecting a single sample at a single time point was poor [53]. Our study collected salivary cortisol at multiple time points on the same day (0, 30, 45, and 60 min after awakening; 11 p.m.) to observe changes in the cortisol awakening response and nocturnal cortisol level associated with Tai Chi intervention.

Moreover, a return visit at 12 weeks after the end of the intervention was conducted to observe the long-term effects of Tai Chi training on young adults with subthreshold depression.

However, this trial may have some potential limitations. Firstly, it is difficult for people involved in RCT to become blind in a non-pharmacological trial [54]. Coaches and participants cannot be blinded in this study. Tai Chi coaches cannot be involved in recruiting, evaluating outcomes, or analyzing data in this study while performance discrepancies may be inevitable. Besides, this study used a randomized trial design and random assignment concealment. Random allocation is the responsibility of independent non-evaluators. Outcome assessors and statistical analysts were blinded to guarantee the test results authenticity and objectivity. Moreover, the project leader retained test quality control staff, and assessors and data analysts retained results until the end of the entire study period. Secondly, all participants came from the same city, contributing to reducing the sample representativeness.

To sum up, this study is the first randomized controlled trial to systematically evaluate the influence of traditional Tai Chi for patients with subthreshold depression from the perspective of subjective and objective indicators. If this trial exhibits significant results, a shred of rigorous evidence could be provided for the application of Tai Chi training among young adults with subthreshold depression, as well as a new way to prevent and reduce the global burden of MDD.

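### Blinded assessment is claimed for all outcomes, but PHQ-9, one of two primary outcomes and the basis of the sample size, is self-reported by participants who know their arm

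*Protocol article*

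**What the plan says.** - **Blinding of assessment.** Outcome measurement says: "All outcomes are evaluated by the experienced assessors who do not know the allocation results of participants". Study design calls the trial single-blind, with outcome assessors and data analysts blinded. The Discussion presents the blinding of assessors and analysts as what secures genuine and objective results.
- **Primary outcomes.** These are the changes in PHQ-9 and HAMD-17 from baseline to 12 weeks. Of the first, Primary outcome measures says: "The 9-item Patient Health Questionnaire (PHQ-9) is a self-report measure used to assess 9 depressive symptoms". Under Secondary outcomes measures, GAD-7 is also described as a self-report scale.
- **Knowledge of allocation.** Randomization and allocation concealment says: "The eligible participants were informed of their allocation result by the independent research assistants via telephone". Blinding says that "it is impossible to blind the Tai Chi coaches and participants", and the Discussion repeats: "Coaches and participants cannot be blinded in this study".
- **Comparator.** The waiting list group is "requested to maintain their routine lifestyle and did not take any intervention measures".
- **Sample size.** Both primaries were considered, and "this study chose PHQ-9 as a basis to estimate the sample size of this study".

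**The concern.** On a self-report scale the respondent is the rater. If the respondent knows the arm, blinding the staff does not blind the rating. The statement covering all outcomes therefore claims a protection that one of the two primary outcomes does not have, and the Discussion then relies on that protection.

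The design makes this matter. One arm attends supervised classes three times a week and the other knowingly waits. Expectation of benefit in the first and disappointment in the second would both widen the PHQ-9 difference in favour of Tai Chi. A reader who takes the blinding statement at face value would give a PHQ-9 difference more weight than the design supports.

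**Working it through.** **1. The statements side by side**

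| Outcome | Role | Who supplies the rating, per the article | Can the rating be blind? |
|---|---|---|---|
| PHQ-9 | Primary; sets the sample size | Participant (stated self-report) | No |
| HAMD-17 | Primary | Described as a clinical evaluation scale, not as self-report | Yes, if the assessor is kept unaware; the interview still draws on what participants say |
| GAD-7 | Secondary | Participant (stated self-report) | No |
| CES-D, CPSS, PSQI | Secondary | Mode of completion not expressly stated | Depends on the mode |
| Salivary cortisol, MRI | Exploratory | Laboratory and scanner | Readout yes |

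The statement fails for at least one primary and one secondary outcome.

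**2. Which outcome sets the sample size**

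Inputs are from Sample size estimation, with the two-sided 5% level from Statistical analyses. The method is a two-sample t test with equal arms and 90% power, using the noncentral t distribution.

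- PHQ-9: pooled SD = √((2.18² + 2.52²)/2) = 2.356. The difference is 8.10 − 6.03 = 2.07, so d = 2.07/2.356 = 0.879. This needs 29 per arm, 58 in total (power 0.908), as stated.
- HAMD-17: pooled SD = √((5² + 7²)/2) = 6.083. The difference is 15 − 9 = 6, so d = 6/6.083 = 0.986. This needs 23 per arm, 46 in total (power 0.905), as stated.

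Both figures reproduce, and PHQ-9 governs. The planned 64 is within one participant of 58/0.9 = 64.4, rounded up to 65. The sample size is not in dispute here.

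**3. What a reporting difference could do (illustration)**

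The documents give no size for reporting bias, so a range *b* of 0.25 to 1.0 point is assumed. Take 29 per arm, SD 2.356 and no true effect. The noncentrality is (*b*/2.356) × √(29/2), and the chance of p < 0.05 follows from the noncentral t with 56 degrees of freedom.

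| Assumed *b* (points) | Share of the planned 2.07 | *b*/SD | Chance of p < 0.05 with no true effect |
|---|---|---|---|
| 0 | 0% | 0 | 5% |
| 0.25 | 12% | 0.106 | 7% |
| 0.5 | 24% | 0.212 | 12% |
| 0.75 | 36% | 0.318 | 22% |
| 1.0 | 48% | 0.424 | 36% |

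The SD is the plan's own, for scores after training. The SD of change from baseline is not given.

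**The case against.** **Disclosure.** The article does not hide the lack of participant blinding. Study design says single-blind, and the Discussion lists unblinded participants as its first limitation. The Discussion also names the Hawthorne effect and low mood among controls as possible confounders. It offers contact with controls as mitigation, together with a mix of subjective and objective measures, and it counts the scales as subjective. This stands, and a reader who inferred concealment would be wrong. What remains is that none of these passages is tied to PHQ-9. The mitigations do not blind its answers, and the objective measures named, MRI and cortisol, are exploratory.

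**A milder reading.** Evaluators collect data on paper forms, so the statement may mean only that blinded staff administer and score every instrument. On that reading it is imprecise rather than untrue. It still gives no protection to the answers.

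**Stronger inferences that the documents do not support.**
- A reader might infer that HAMD-17 should lead, with PHQ-9 tested after it, at no cost in patients. At 29 per arm, power for HAMD-17 is 0.958 if d = 0.986. But that effect comes from patients with major depressive disorder, whom this trial excludes. If d were 0.7, 0.6 or 0.5 (assumptions), power at 29 per arm would be 0.75, 0.61 or 0.46, and 90% power would need about 44, 60 or 86 per arm. The PHQ-9 inputs come from a subthreshold sample. Re-ranking is therefore a trade-off, and in a trial already started it is a substantive amendment.
- A reader might infer that the trial can be declared positive on PHQ-9 alone. The article gives no rule for combining the two primaries, and a statistical analysis plan may supply one.
- A reader might infer that HAMD-17 is free of the problem. It is better protected but not immune, because its ratings depend partly on what unblinded participants report.

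**Conclusion.** The point holds as a correction to the blinding claim. Blinded assessment, stated for all outcomes, does not apply to PHQ-9 or GAD-7, and the objectivity claim in the Discussion cannot extend to them. This rests on the article's own text and needs no outside figure.

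How much it matters depends on a reporting bias that the documents do not quantify. The range above shows that a bias well below the planned difference could matter; it does not show that such a bias exists. A self-report primary outcome is legitimate. The fault lies in describing it as blind-assessed. The correction should be made because PHQ-9 is primary and sets the sample size, but it does not invalidate the design or alter any stated number.

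**What to change.** - In Outcome measurement, limit the blinded-assessment statement to HAMD-17 and the laboratory and imaging readouts. Limit the objectivity statement in the Discussion in the same way.
- State that PHQ-9, GAD-7 and any other self-report scale are rated by participants who know their arm, and give the mode of completion for CES-D, CPSS and PSQI. Blinded administration and scoring can still be mentioned as such.
- State that a PHQ-9 difference will not be reported as blind-assessed and will be interpreted alongside the assessor-rated HAMD-17, noting that HAMD-17 is better protected but not immune.

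The cost is a few sentences, with no change to the sample size, the visits or the order of the primaries. The downside is that a result seen on PHQ-9 only would carry a weaker claim.

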#### Primary outcome measures

The primary outcome measure changes in the PHQ-9 and HAMD-17 between baseline and 12 weeks.

The 9-item Patient Health Questionnaire (PHQ-9) is a self-report measure used to assess 9 depressive symptoms according to the DSM-IV depression criteria. It has a total of 9 items, each with a score of 4 points (0–3 points) and the total scores’ range of 0–27 points. This score can be used to describe the patient’s symptoms, divided into five categories: none (0–4), mild (5–9), moderate (10–14), moderately severe (15–19), and severe (20–27) [41]. PHQ-9 has been translated into Chinese, and its Chinese version has demonstrated reliability and validity [42].

The 17-item Hamilton Depression Scale (HAMD-17) [43] is the most widely used scale in the clinical evaluation of depression, including17 items that assess function in five areas: anxiety/somatization, retardation, cognitive impairment, sleep disturbance, and weight change. Higher scores indicate more severe depression.

#### Secondary outcomes measures

Center for Epidemiological Studies Depression Scale (CES-D) [44] designed to measure the frequency of depression-related symptoms in a subject over the past week. It is a 4-point ordinal scale: rarely or none of the time (< 1 day); some or a little of the time (1–2 days); occasionally or a moderate amount of the time (3–4 days); and most or all of the time (5–7 days). CES-D score was between 0 and 60, with higher scores indicating greater symptom burden. The cut-off score of CES-D was 16, indicating significant or mild depression [39].

Chinese Perceived Stress Scale (CPSS) [45] is applied to assess the stress, consisting of 14 items to reflect the uncontrollability and tension of stress. Each item ranges from 0 (never) to 4 (very often). Higher aggregate scores express greater perceived stress.

A 7-item Generalized Anxiety Disorder (GAD-7) [46] is a self-report scale designed to measure the frequency of anxiety symptoms in the past 2 weeks. It is composed seven items, and each item score ranges from 0 (not all) to 3 (almost daily); 5 points, 10 points, and 15 points represent thresholds for mild, moderate, and severe anxiety symptoms.

Pittsburgh Sleep Quality Index (PSQI) is used to measure the quality of sleep [47]. The Chinese version of PSQI has been reported acceptable internal consistency, test-retest reliability, construct validity, and criterion-related validity. The questionnaire has nineteen individual items used to generate seven composite scores. The results provided numbers in seven categories: subjective sleep quality, sleep latency, sleep duration, habitual sleep efficiency, sleep disturbances, use of sleeping medication, and daytime dysfunction. The sum of the seven component scores ranges from 0 to 21; higher scores indicate poorer subjective sleep quality [48].

#### Exploratory outcomes measures

Saliva cortisol levels assess to evaluate the functional status of the HPA axis (Cortisol Awakening Response (CAR) and nocturnal cortisol level). Saliva was collected using the Salivette sampling device (Sarstedt, Italy). The Salivette sampling device was distributed to the subjects before the collecting day. Besides, the subjects were instructed to ensure that they fully understand the methods and precautions of saliva collection. Subjects collected saliva at home or dormitory at 0, 30, 45, and 60 min after awakening and 23:00 before sleeping and were asked to avoid eating, drinking alcohol or coffee, brushing teeth, smoking, or exercising within 60 min after waking and 30 min before other saliva collections. Do not collect samples when oral diseases, inflammation, or lesions exist (blood contamination). The subjects would chew the polyester swab of the Salivette sampling device for at least 1 min and then put the polyester swab back into the inner tube of the Salivette sampling device. These devices were sent to the laboratory as soon as possible. Saliva samples recovered from a polyester swab by centrifugation at 3000 rpm for 15 min. Then, clear saliva was obtained in the outer tube and frozen at − 80 °C until analysis. Salivary cortisol concentrations were determined using a salivary cortisol ELISA kit (DRG Diagnostics, Germany). The inter-assay coefficient of variation was less than 13.6%, and intra-assay coefficient of variation was less than 6.1%, with a minimum detectable concentration of 0.09 ng/ml.

Structure and function of related brain regions were measured using functional magnetic resonance imaging (*f*MRI), which is a non-invasive method for examining brain activity and structure. T1-weighted structural images were acquired with the three-dimensional magnetization-prepared rapid acquisition gradient-echo (3DMPRAGE) sequence (sagittal scanning, TR/TE/FOV = 2000 ms/1.73 ms/240 mm × 240 mm, flip angle (FA) = 15 degrees, layers = 160, layer thickness = 1 mm, imaging matrix = 256 × 256). The resting-state sequence was performed (axial (nonoblique), TR/TE/FOV = 2000 ms/30 ms/220 mm × 220 mm, flip angle (FA) = 90 degrees, layers = 37, layers = 3.5 mm, imaging matrix = 64 × 64, time points 180). The fMRI scan was measured by professional operators at the Affiliated Rehabilitation Hospital of FJTCM using a 3.0-T signal MRI scanner (GE Healthcare, Little Chalfont, UK) with a birdcage head coil. MR scanning was performed at baseline and end of the intervention period (12 weeks after randomization).

### Safety evaluation

During the study intervention, any adverse events of the subject will be monitored, recorded in the adverse event case report form, reported to the research assistant, and analyzed for causality related to Tai Chi training and the severity of the adverse event.

During the intervention, any adverse events (defined as any functional impairment caused by the intervention, such as knee or ankle sprain, increased depression, knee pain, hypoglycemia) will be recorded on the case report form (CRF). If any adverse event occurs, the coaches or project managers will provide the corresponding treatment to the participant. Serious adverse events should be filled in a report form and reported to the Ethics Committee of Fujian University of Traditional Chinese Medicine Subsidiary Rehabilitation Hospital immediately.

Based on various factors, the safety evaluation of the subjects is conducted. The evaluation results are divided into level 1 (safe, without any adverse reactions); level 2 (safer, with mild adverse reactions, no need to do any treatment, subjects can continue to participate in training); level 3 (have safety problems, have moderate adverse reactions, and subjects can continue training after treatment); and level 4 (the study was discontinued due to serious adverse reactions) *(Common Terminology Criteria for Adverse Events (CTCAE) Version 5.0, US Department of Health and Human Services, 2017).*

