### Withdrawal or dropout criteria

Participants will withdraw from this trial according to the following:
Participants who decide to withdraw.Development of serious diseases hinders the continuation of the trial.Suffering from a serious adverse event (AE) related to the Tai Chi training.Participations in the waiting list group have regularly engaged in Tai Chi exercise.

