## Discussion

It is widely believed in the academic community that practicing Tai Chi is of great benefit to promoting and maintaining physical and mental health [17]. Previous studies have demonstrated that Tai Chi may reduce depressive symptoms and related symptoms such as stress and insomnia in patients with depression [16, 21]. However, the treatment effect of traditional Tai Chi alone on subthreshold depression remains unclear.

In this experiment, a rigorous random, parallel control design was conducted to observe the effectiveness and safety of Tai Chi training on subthreshold depression patients. Furthermore, the physiological effect of the action of Tai Chi was further explored by observing the cortisol level (HPA axis function) and neuroimaging (*f*MRI). This study provides evidence that Tai Chi can treat subthreshold depression.

The control group was set as the waiting list group, and there may be some confounding factors, such as the Hawthorne effect and bad mood of the control group.

The “Hawthorne effect” refers to the effect of deliberately changing some behaviors or verbal expressions when people realize that they are being paid attention to or observed. First, in this study, the researchers maintained their attention and communication with the control group by recording weekly activity logs and regularly holding some entertainment activities to minimize the influence of confounding factors in the waiting list group on the research results. Second, in the evaluation of this study, subjective and objective outcome indicators (such as scales, MRI, and cortisol) were used to detect the study participants to reduce the bias of confounding factors.

To improve the quality of the research, some methods were employed in this study. Senior physical education teachers are arranged as Tai Chi training coaches to ensure the standard of the patient’s Tai Chi training. The participant in the Tai Chi group gathered at a fixed place and time to practice. To control the bias caused by the amount of exercise, all participants were required to record activity logs. Besides, Tai Chi training was supervised by two research assistants to guarantee that both the coaches and the participants practice carefully.

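### The safety section builds causation into its definition of an adverse event but also plans to assess causality afterwards; read literally, the definition leaves the waiting-list arm with nothing to record

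*Protocol article*

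**What the plan says.** All references are to the protocol article.

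- **Safety evaluation, first paragraph.** "During the study intervention, any adverse events of the subject will be monitored, recorded in the adverse event case report form". The events are then "analyzed for causality related to Tai Chi training and the severity of the adverse event". No arm is named, and causality is judged after recording.
- **Safety evaluation, second paragraph.** What goes on the case report form is "any adverse events (defined as any functional impairment caused by the intervention, such as knee or ankle sprain, increased depression, knee pain, hypoglycemia". This is the only definition of an adverse event in the article.
- **Safety evaluation, grading.** The four levels are worded in terms of adverse reactions, and the middle two in terms of carrying on with training, for example "level 2 (safer, with mild adverse reactions, no need to do any treatment, subjects can continue to participate in training".
- **Withdrawal or dropout criteria.** One criterion is "Suffering from a serious adverse event (AE) related to the Tai Chi training". Relatedness is a qualifier added to an adverse event, not part of what makes it one.
- **Waiting list group.** These participants "did not take any intervention measures".
- **Follow-up period.** After week 12, "all participants will begin an additional 12 weeks of unsupervised follow-up period". Only the primary and secondary outcomes are named for remeasurement at its end.
- **Discussion.** The randomised parallel-control design is said to serve "to observe the effectiveness and safety of Tai Chi training on subthreshold depression patients".

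**The concern.** A controlled statement about safety needs events to be ascertained in the same way in both arms, with cause judged separately. If cause is a condition of entry, the later causality assessment has nothing left to decide. Two investigators following the same section could also fill in different forms: one records every event, the other only events already blamed on Tai Chi.

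The examples in the definition make this concrete. Increased depression and knee pain can arise without any training. Under the definition they count only if someone attributes them to Tai Chi. Participants and coaches cannot be blinded (Blinding section), so that attribution is open to error in either direction: too many background events credited to Tai Chi, or true reactions dismissed and never written down. The same paragraph sets out serious-event reporting to the ethics committee, so the narrow definition could carry over to that as well.

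Both collection sentences are also tied to the intervention period. Participants stay in the trial to week 24, so for 12 of 24 weeks no adverse event collection is stated.

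**Working it through.** The article states no safety figure, so there is nothing to reproduce. The check is mainly textual, with one illustration.

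**Step 1. Compare the two paragraphs of Safety evaluation.**

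| Question | First paragraph | Second paragraph |
|---|---|---|
| Which events are recorded? | Any event of the subject | Functional impairment due to the intervention |
| When is cause judged? | After recording | As a condition of being an event |
| Can a control have one? | Yes, no arm is excluded | No, controls receive no intervention |
| Period | Intervention | Intervention |

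The first three rows cannot all be satisfied by one rule, and nothing in the article says which paragraph governs. The withdrawal criterion sides with the first paragraph. The grading scale fits only people who are training, so it sides with the second.

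**Step 2. Time window.** The intervention period can be read as the 12 weeks common to both arms, so the window by itself does not exclude controls. What it leaves out is weeks 12 to 24, in both arms.

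**Step 3. Illustration of size.** Inputs: 32 per arm (Sample size estimation), and an assumed background risk p over 12 weeks, equal in both arms. The article gives no p, so a range is shown. Suppose the second paragraph is applied literally to controls (0 of 32 recorded) while every event in the Tai Chi arm is attributed to training and recorded.

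- Expected participants with an event per arm: 32 × p.
- Chance that 32 controls would truly have none: (1 − p)^32.
- Two-sided Fisher exact p-value for x/32 versus 0/32: 2 × C(32,x)/C(64,x). For x = 3 this is 2 × 4,960/41,664 = 0.24. For x = 5 it is 0.053. For x = 6 it is 2 × 906,192/74,974,368 = 0.024. So 6 versus 0 is the first split below 0.05.
- Chance of 6 or more events in the Tai Chi arm with no true difference: the binomial tail with n = 32 and risk p.

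| Assumed p | Expected events per arm | P(no event among 32 controls) | P(6 or more in Tai Chi arm) |
|---|---|---|---|
| 5% | 1.6 | 19% | 0.5% |
| 10% | 3.2 | 3.4% | 9% |
| 20% | 6.4 | 0.08% | 64% |
| 30% | 9.6 | 0.001% | 95% |

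At a low background risk the literal rule would rarely produce a nominally significant false difference. At 20% or more it usually would. This is the extreme case for over-attribution. With under-attribution the counts shrink towards 0 versus 0, and real reactions are lost.

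**The case against.** The strongest reply is that the first paragraph already does what is needed: any event of the subject is recorded and causality comes later. On that reading the second paragraph is loose drafting and controls can have events. This stands as far as it goes. A reader might infer that the waiting-list arm cannot have adverse events at all, or that its count is fixed at 0 of 32, but the article does not support that. It holds only if the second paragraph is applied and the first ignored. What remains is that the article's only explicit definition conflicts with the paragraph before it.

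A reader might also conclude that the safety comparison is void. No between-arm safety test is specified: Statistical analyses ties the intention-to-treat and per-protocol analyses to the primary and secondary outcomes, and safety is not among the listed outcomes. There is no planned test to invalidate. What is weakened is a controlled statement on safety of the kind the Discussion makes.

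Nor does worsening depression in controls go unmeasured. PHQ-9, HAMD-17 and CES-D are scheduled in both arms at baseline, week 12 and week 24. That limits the loss for this one example. It does not cover sprains, knee pain or hypoglycaemia, and a score change is not an adverse event record.

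Finally, a condensed article may leave safety procedures to the full protocol, and the Quality control section mentions a research manual and a case report form. That would answer an omission, and it tempers the point about weeks 12 to 24. It does not answer a definition that the article states and then contradicts.

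**Conclusion.** The point holds as an internal contradiction with a real consequence. The definition makes causation a condition for being an adverse event, while the preceding paragraph and the withdrawal criteria treat it as a later, separate judgement. Applied literally, the definition removes waiting-list events and makes Tai Chi events depend on unblinded attribution, so the Discussion's claim to observe safety with a parallel control would not be supported. No collection is stated for weeks 12 to 24.

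The size is illustrative only: about 1.6 to 9.6 of 32 controls with excluded events at assumed equal background risks of 5% to 30%. It rests on those assumed risks and on literal use of the second paragraph. Randomisation, sample size and the efficacy analyses are not affected.

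**What to change.** Reconcile the two paragraphs with one definition that does not mention cause: any untoward occurrence after randomisation, in either arm. Then:

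- ask the same adverse event questions in both arms at the existing week-12 and week-24 visits, and use the activity logs that all participants already keep;
- record relatedness to Tai Chi afterwards, as a separate item;
- say how the four-level grading is to be read for participants who are not training;
- state that collection runs to week 24;
- report events by arm, with related events as a subset.

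The cost is a revised definition and one added case report form question at visits already planned. If data collection has finished, the definition can no longer be changed. The trial report should then state how events were actually ascertained in each arm and over what period, and should make no controlled safety claim unless ascertainment was the same in both.
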